## Abstract

**Background:**

Norwegian Psychomotor Physiotherapy (NPMP) has been an established treatment approach for more than 50 years, although mostly in the Scandinavian countries, and is usually applied to patients with widespread and long-lasting musculoskeletal pain and/or psychosomatic disorders. Few studies have been investigating outcome of NPMP and no randomized clinical trials (RCT) have been systematically tried out on individuals.

**Methods/design:**

This is a study protocol for a pragmatic, single blinded RCT, which will take place in a city of Norway. The participants will be block randomized either to receive NPMP or Cognitive Patient Education in combination with active individualized physiotherapy (COPE-PT). The intervention will reflect usual care and will be conducted in physiotherapy clinics by five experienced physiotherapists in each of the two treatment approaches.

**Discussion:**

The findings of the present study may give an important contribution to our knowledge of the outcome of NPMP, on patients with long-lasting widespread musculoskeletal pain and/or pain located to the neck and shoulder region.

**Trial registration:**

The study has been registered with ClinicalTrials.gov (June 9 th 2015, NCT02482792).

**Electronic supplementary material:**

The online version of this article (doi:10.1186/s12891-016-1159-8) contains supplementary material, which is available to authorized users.

## Background

Musculoskeletal pain affects about three in four of the adult population in Norway during 1 month, and is most common among women, increase with age and prevalence seems to be stable over time [1, 2]. Long-lasting-, as well as widespread musculoskeletal pain also seem to be common [1, 3]. Musculoskeletal pain comprises nearly 40 % of sick leave in Norway [4] and 32 % of the disability pensions [5]. Because of the complexity and multi-factorial etiology of long-lasting musculoskeletal pain, targeted treatment is challenging and time consuming with a need of including physical, psychological and social aspects in the intervention [6, 7].

Norwegian Psychomotor Physiotherapy (NPMP) has been an established treatment approach for more than 50 years, although mostly in the Scandinavian countries. NPMP is usually applied to patients with widespread and long-lasting musculoskeletal pain and/or psychosomatic disorders. The perspective in NPMP is that physical, psychological and social strains may influence the whole body and can affect muscle tension, breathing, posture, balance, movements and flexibility. These elements are addressed when grasping the patient’s history of complaints, as well as during body examination and treatment [8]. The majority of patients referred to NPMP are women, their health problems have often lasted for several years and the treatment might be long-lasting because of the complexity of the pain disorder [9, 10].

Most studies of NPMP have focused on descriptions of different aspects in the treatment process, both from the patient’s and the physiotherapist’s perspective [11–16].

There are few studies investigating the outcome of NPMP treatment. However, Aabakken et al. [17] did a one-group prospective study of 152 patients with chronic pain receiving NPMP. After two and a half years, 72 % of the patients had achieved significant improvement regarding pain symptoms and everyday coping. In another prospective study [18] 60 patients with long-lasting musculoskeletal pain were included; 40 received NPMP and 20 were on a waiting- list for such treatment. After 12 months the 40 patients experienced reduced depression, anxiety, insomnia, fatigue and improved quality of life, while the patients on a 6 months waiting list had not changed. Only one RCT of NPMP has been performed, although only for groups and not on individuals, following a multi-model treatment program for patients with long-lasting musculoskeletal pain [19]. The study indicated that the patients receiving NPMP group treatment achieved fewer tender points, reduced distribution of pain and a higher rate of return to work after 1 year, compared to a control group of patients receiving usual follow-up at an out-patient rehabilitation clinic. However, the drop-out in the treatment group was large, making the results questionable. Another one-group prospective observational study of patients with low back pain receiving NPMP, showed that nine of the 12 included patients improved significantly regarding pain, flexibility and ability to relax [20].

In summary, few studies have been investigating outcome of NPMP and no RCT of the treatment approach have been systematically tried out on individuals.

### Purpose and research question

The main aim of the present study is to investigate the effectiveness of Norwegian Psychomotor Physiotherapy (NPMP) on pain, physical function, mental health, quality of life and sick leave in employees with long-lasting musculoskeletal pain or pain located to the neck and shoulder region, compared to employees receiving Cognitive Patient Education in combination with active individualized physiotherapy (COPE-PT).

The following research questions are posed:Is there a difference in pain intensity between workers who have received Norwegian Psychomotor Physiotherapy (NPMP) compared to those receiving Cognitive Patient Education and active, individualized physiotherapy (COPE-PT) at 3, 6 and 12 months after inclusion in the study?

Furthermore, do workers receiving NPMP improve more in function, mental health and quality of life, compared to those receiving COPE-PT at 3, 6 and 12 months after inclusion in the study?Is there a difference in sick leave 12 months after inclusion in the study between workers receiving NPMP, compared to the sick-listed COPE-PT participants?What characterizes those who are still sick-listed at 12 months compared to those who have returned to work? Is there an association between the tested function and self-reported measures on health and working ability?

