### Participants

Employees working in the Municipality of Bergen with long-lasting widespread musculoskeletal pain or pain in the neck and shoulders, are invited to participate in the study. They can have had several short sick-leaves during the last 2 years, or been sick-listed fulltime for < 6 months, or still be working despite their pain. The employees will get information about the project through their supervisors/work place leaders and/or through pamphlets at work. It is voluntary to participate and those who are interested will call for an appointment for an evaluation. On the first visit demographic data is collected and the participants will fill in questionnaires and undergo an examination of physical function (Tables 1 and 2). Those who fulfill the inclusion criteria will be invited to participate in the RCT (Fig. 1). Those not fulfilling the criteria (too little pain and functional problems) will get individual feedback and advice. Informed consent is first signed before the functional testing starts and then, once more in the same consultation before randomization if they fulfil inclusions criteria and want to participate in the RCT.

**Table 1 Tab1:** Description of the questionnaires used at baseline, 3 months, 6 months, and 12 months follow-up

Questionnaire	Content	Scores
^a^Numeric Pain Rating Scale (NPRS)	Pain intensity	Numeric scale from 0–10. A change ≥ 2 on NPRS indicates meaningful change.
^a^Neck Disability Index (NDI) (Vernon et al. 1991 [27])	Disability due to neck pain.10 items	Each item is scored from 0 – 5, higher score indicating worse function. Maximum score is 50. A change > 5 points or 10 % is clinically meaningful.
^a^Shoulder Pain and Disability Inventory (SPADI) (Williams et al. 1995 [28])	Pain (5-item) Disability (8-item) 13 items	Each item is scored on a numeric rating scale ranging from 0 to 10. Mean value from the combined scores is given in percent (0–100), higher scores indicating more pain and disability. A change ≥10 on SPADI indicates clinical important change.
^a^Örebro Musculoskeletal Pain Questionnaire -short form (ÖMPQ-SF) (Linton et al. 2011 [26])	Risk for future work disability 10 items	Numeric scale from 0–10, from ‘no pain’ to ‘pain as bad as it could be’ or ‘completely disagree’ to ‘completely agree’. Three items are reversed. The items are being summarized. The total score ranges from 1 to 100 where higher scores indicate higher estimated risk for future work disability.

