#### Exclusion criteria

Sick-listed more than 6 months continuously

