#### *Questionnaires* (Table 1)

The *Örebro Musculoskeletal Pain Questionnaire short form (ÖMPQ-SF)* has shown to predict the risk for future work disability. The short form with 10 items is appropriate for clinical and research purposes, and is nearly as accurate as the longer version [26].

The *Neck Disability Index (NDI)*, measures disability due to neck pain, and is a modification of the Oswestry Disability Index [27]. Good reliability and validity of NDI have been demonstrated [27].

The *Shoulder Pain and Disability Inventory (SPADI)* [28], is developed to measure current shoulder pain and function. SPADI has shown to have good reliability, good construct validity [29], to be responsive to change over time in a variety of patient populations, and is able to discriminate adequately between patients with improving and deteriorating conditions [29, 30].

The *Norwegian Function Assessment Scale (NFAS)*, is questioning work-related functioning with basis in the ICF’s classification system [31]. Test-retest reliability has been tested in a normal population and found acceptable [32].

*Subjective Health Complaints Inventory (SHC)* consists of items regarding subjective somatic or psychological complaints experienced during the last month. The SHC inventory has shown satisfactory test-retest reliability in students and patients with LBP [33].

The *Hopkins Symptoms Checklist (HSCL-25)* measures anxiety and depression symptoms. The HSCL has been shown to have satisfactory validity and reliability in psychiatric outpatients and in a normal population [34].

The *Tampa Scale of Kinesiophobia (TSK)* [35] in short form measures fear of movement and re-injury. The TSK has been validated in numerous studies including patients with neck pain, acute and chronic LBP and fibromyalgia [35–38].

The *Short Form-12 (SF-12)*, which is a 12-item version of the SF-36, measure physical and mental health-related quality of life [39]. The SF-12 has shown good internal consistency, validity, and responsiveness in patients with LBP [40].

The *Bergen Insomnia Scale (BIS)* measures sleep disturbance. BIS can refer to high internal consistency, adequate reliability and good convergent and discriminative validity [41].

Sick leave will be measured by number of self-reported days of absence from work.

At 3 and 6 months the patients in both arms of the RCT will also fill in the *Client Satisfaction Questionnaire (CSQ-8)* [42].

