### Randomization method

Block randomization of the study sample will be employed, using a computer generated list with blocks of six to ensure similar number of participants in both intervention groups. Information about intervention allocation (A or B) is then put into premade and ordered envelopes. The sealed envelopes are kept in a locked box by receptionists who have no information about the content. The receptionist hands out one envelop consecutively to the participants after eligibility and baseline measurements. The envelope contains information regarding treatment and names of treating therapists (A or B), and the participants are invited to call one of them for an appointment.

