### Statistical analysis

All statistical analyses will be carried out using R version 3.2.5 (The R Foundation for Statistical Computing, www.r-project.org) and SPSS version 24 (SPSS Inc., Chicago, IL, USA) for windows. All tests will be two-sided, and *p* values less than 0.05 will be considered statistically significant.

Continuous variables will be reported as means ± SEM and categorical variables as percentages (%) ± SEM. The chi-square test will be used to test for group difference in percentages of categorical variables, while the two-sample *t*-test will be used to test for group difference in means of continuous variables. Analog non-parametric tests will be evaluated when strongly skewed distributions.

To estimate and compare the treatment effect of the two specific interventions at the four time points (baseline, 3, 6 and 12 months) we will use mixed effects models. All models will define treatment, time and treatment-by-time interaction as fixed effects, whereas a random intercept will be specified to account for correlated observations of the same individual (an exchangeable correlation structure assumed). Depending on the measurement level of the outcome under study, treatment effects will be presented as relative estimates (e.g., odds ratios, relative risk) or predicted mean differences with 95 % confidence intervals, corrected for multiple testing. Age, gender, body mass index, duration of pain and work status will be evaluated as additional adjustment variables.

We cannot exclude the possibility that missing outcome data may occur for a proportion of participants. The mixed effects model will produce unbiased effect estimates as the model uses a likelihood-based estimation procedure, provided the data are missing at random (MAR). Additionally, a multiple imputation method for missing data will be utilized if missing data occur in covariates as well.

Effect size (ES) for mean change will also be calculated by subtracting post-test scores (6 and 12 months) from baseline in the two groups, dividing it by the standard deviation (SD) of the change score.

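### As worded, the sick-leave question compares NPMP workers with only the sick-listed part of the COPE-PT arm, contradicting the main aim

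*Protocol article*

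**What the plan says.** All references are to the protocol article.

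- **Purpose and research question, sick-leave question.** The difference in sick leave at 12 months is sought "between workers receiving NPMP, compared to the sick-listed COPE-PT participants".
- **Same section, main aim.** Sick leave is one of the listed outcomes, and NPMP is "compared to employees receiving Cognitive Patient Education in combination with active individualized physiotherapy (COPE-PT". There is no sick-list restriction.
- **Same section, question on function, mental health and quality of life.** NPMP is "compared to those receiving COPE-PT at 3, 6 and 12 months after inclusion in the study", again unrestricted.
- **Participants.** People may enter after several short sick leaves, or while sick-listed full time for less than 6 months, "or still be working despite their pain".
- **Exclusion criteria.** The only criterion is "Sick-listed more than 6 months continuously".
- **Secondary outcomes, Questionnaires.** "Sick leave will be measured by number of self-reported days of absence from work". No population is attached to this outcome.
- **Randomization method.** The list uses "blocks of six to ensure similar number of participants in both intervention groups". Stratification by work status is not mentioned.
- **Statistical analysis.** The mixed models have fixed effects for arm, time and their interaction. No sick-listed subset is defined, and work status is only a candidate adjustment variable.

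**The concern.** Both arms can contain people who are not sick-listed at entry. The sick-leave question removes them from the COPE-PT side and, as worded, leaves them in on the NPMP side. The two groups then differ in work status by construction, and a difference in sick leave could appear with no difference in treatment effect.

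The question also does not say when a participant must be sick-listed to count. If it means at entry, the comparator is selected on a likely prognostic factor. If it means at 12 months, the comparator is selected on the outcome itself.

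Sick leave is named in the main aim, so readers will look for this result. With two incompatible comparators in one section, the choice between them could be made after the data are seen.

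**Working it through.** **Plan's own figure.** The document gives no rate, effect size or sample size for sick leave, so there is none to reproduce. The arm size used below, 64, comes from the Sample size calculation for pain. It does reproduce: a 1-point difference with SD 2, 80% power and two-sided 5% needs 63 per group by the normal approximation and 63.8, so 64, by the t-test.

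**Inputs for the illustration.** All three are assumptions, because the document states none of them:
- s, the share sick-listed at entry, the same in both arms: 20% to 80%.
- a, the proportion sick-listed at 12 months among those sick-listed at entry: 30% to 50%.
- b, the same proportion among those not sick-listed at entry: 10%.

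**Formula with identical treatments.**
- NPMP, whole arm: s·a + (1 − s)·b.
- COPE-PT, only those sick-listed at entry: a.
- Expected difference: s·a + (1 − s)·b − a = (1 − s)(b − a).

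This is below zero, in favour of NPMP, whenever a > b and s < 1. It is zero if a = b.

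**One case in full.** With s = 40%, a = 40% and b = 10%:
- NPMP: 0.40 × 0.40 + 0.60 × 0.10 = 0.22.
- COPE-PT, sick-listed: 0.40.
- Difference: 0.22 − 0.40 = −0.18; check: 0.60 × (0.10 − 0.40) = −0.18.

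**Range.** Each cell gives NPMP % v COPE-PT %, then the difference in percentage points. In brackets is the share of simulated trials with a false significant result for NPMP (64 per arm; 13, 26, 38 or 51 COPE-PT participants sick-listed; pooled z-test, two-sided 5%; 20,000 replicates).

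| s | a = 30% | a = 40% | a = 50% |
|---|---|---|---|
| 20% | 14 v 30, −16 (31%) | 16 v 40, −24 (49%) | 18 v 50, −32 (69%) |
| 40% | 18 v 30, −12 (26%) | 22 v 40, −18 (44%) | 26 v 50, −24 (61%) |
| 60% | 22 v 30, −8 (15%) | 28 v 40, −12 (25%) | 34 v 50, −16 (38%) |
| 80% | 26 v 30, −4 (7%) | 34 v 40, −6 (10%) | 42 v 50, −8 (13%) |

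**Controls.**
- With a = b = 20%, the expected difference is 0 and the two-sided error is about 4–5%.
- Comparing both whole arms, the expected difference is 0 and the error is about 3–5%.
- Restricting both arms to those sick-listed at entry, the expected difference is 0 and the error is about 4–8%, the upper end with only 13 per arm.

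**If sick-listed means at 12 months.** The COPE-PT group is then 100% sick-listed by definition, and the distortion is larger than any in the table.

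**The case against.** The strongest reply is that this is a slip of wording. The main aim has a symmetric comparison, the models in Statistical analysis contain no sick-listed subset, and no analysis line for sick leave carries the restriction. The research question that follows asks who is still sick-listed at 12 months and who has returned to work, which presupposes people sick-listed at entry. The authors may have meant sick-listed participants in both arms, and on that reading the bias is zero. That the NPMP side includes every work status is inferred from the lack of a restriction; the text does not say it. Much of this stands, and it limits what can be claimed. It does not remove the contradiction: comparing whole arms and comparing sick-listed participants in both arms are different analyses, and no section says which is meant.

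Three stronger readings are tempting but not supported:

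- *A reader might infer that the trial plans a biased analysis.* The document specifies no such analysis. It contains one asymmetric question that conflicts with its own main aim.
- *A reader might infer from the word receiving that groups are formed by treatment taken.* The design section says participants are randomised to receive one treatment or the other, and the other between-arm questions use the same verb. This is ordinary phrasing, and the definition of analysis sets is commonly left to a fuller document.
- *A reader might take a figure such as 44% as this trial's error rate.* It depends on assumed rates and on a yes/no status, whereas the protocol counts days of absence.

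**Conclusion.** The point holds as an internal contradiction on a secondary outcome. Followed literally, the sick-leave question is not a randomised comparison. The direction towards NPMP is conditional: it requires that people sick-listed at entry have more later absence than those working. That is plausible, but the document does not quantify it.

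Under the assumed rates the spurious difference runs from 4 to 32 percentage points, with false findings for NPMP in about 7% to 69% of trials. The same argument applies to days of absence, but its size on that scale cannot be derived from the document.

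The primary pain outcome, the sample size and the questions on pain, function, mental health and quality of life are untouched. The right grade is therefore should-fix, not must-fix.

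**What to change.** Reword the sick-leave question so that it agrees with the main aim and keeps the stated time point, for example: *Does sick leave at 12 months after inclusion differ between participants randomised to NPMP and participants randomised to COPE-PT?* Use work status at baseline as an adjustment variable; Statistical analysis already lists work status as a candidate.

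If sick-listed participants are of special interest, add a secondary subgroup analysis that restricts both arms by the same sick-list status at baseline. Status during or after follow-up should not define the groups.

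The cost is the wording of one question and a line naming the covariate. It needs no new data and does not change the sample size.

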## Methods and design

### Design and settings

This protocol describes a pragmatic single blinded randomised controlled study that will take place in a city of Norway. The study will follow the CONSORT 2010 checklist. The participants will be randomized either to receive Norwegian Psychomotor Physiotherapy (NPMP) or Cognitive Patient Education in combination with active, individualized physiotherapy (COPE- PT). In order to reflect usual care, the intervention will be pragmatic and conducted in physiotherapy clinics by five experienced physiotherapists in each of the two treatment approaches (Fig. 1). The study has been registered with ClinicalTrials.gov (June 2015, NCT02482792).

**Fig. 1 Fig1:**
[figure not shown]
Flow diagram of the study protocol

### Participants

Employees working in the Municipality of Bergen with long-lasting widespread musculoskeletal pain or pain in the neck and shoulders, are invited to participate in the study. They can have had several short sick-leaves during the last 2 years, or been sick-listed fulltime for < 6 months, or still be working despite their pain. The employees will get information about the project through their supervisors/work place leaders and/or through pamphlets at work. It is voluntary to participate and those who are interested will call for an appointment for an evaluation. On the first visit demographic data is collected and the participants will fill in questionnaires and undergo an examination of physical function (Tables 1 and 2). Those who fulfill the inclusion criteria will be invited to participate in the RCT (Fig. 1). Those not fulfilling the criteria (too little pain and functional problems) will get individual feedback and advice. Informed consent is first signed before the functional testing starts and then, once more in the same consultation before randomization if they fulfil inclusions criteria and want to participate in the RCT.

**Table 1 Tab1:** Description of the questionnaires used at baseline, 3 months, 6 months, and 12 months follow-up

Questionnaire	Content	Scores
^a^Numeric Pain Rating Scale (NPRS)	Pain intensity	Numeric scale from 0–10. A change ≥ 2 on NPRS indicates meaningful change.
^a^Neck Disability Index (NDI) (Vernon et al. 1991 [27])	Disability due to neck pain.10 items	Each item is scored from 0 – 5, higher score indicating worse function. Maximum score is 50. A change > 5 points or 10 % is clinically meaningful.
^a^Shoulder Pain and Disability Inventory (SPADI) (Williams et al. 1995 [28])	Pain (5-item) Disability (8-item) 13 items	Each item is scored on a numeric rating scale ranging from 0 to 10. Mean value from the combined scores is given in percent (0–100), higher scores indicating more pain and disability. A change ≥10 on SPADI indicates clinical important change.
^a^Örebro Musculoskeletal Pain Questionnaire -short form (ÖMPQ-SF) (Linton et al. 2011 [26])	Risk for future work disability 10 items	Numeric scale from 0–10, from ‘no pain’ to ‘pain as bad as it could be’ or ‘completely disagree’ to ‘completely agree’. Three items are reversed. The items are being summarized. The total score ranges from 1 to 100 where higher scores indicate higher estimated risk for future work disability.
Norwegian Function Assessment Scale (NFAS) (Brage et al. 2004 [31]; Osteras et al. 2007 [32])	39 items in seven domains: walking/standing, holding/picking up something, lifting/carrying, sitting, coping/managing, cooperation/communication, and senses.	Scored on a 4 point Likert scale, ranging from ‘no difficulty’ to ‘could not do it’, and an average score is calculated.
Subjective Health Complaints inventory (SHC)	Experienced somatic or psychological complaints 29 items	Scored on a 4 point Likert scale, ranging from 0 (no complaints) to 3 (severe complaints). Sumscores are calculated, ranging from 0–87.
Hopkins Symptoms Checklist (HSCL-25) (Derogatis et al. 1974 [34])	Anxiety symptoms (10 items) and Depression symptoms (15 items) 25 items	Scores range from 1 to 4, with 4 indicating severe symptoms. Mean score is reported to 1.23 (95 % CI 1.19–1.30) in a normal population, and cut-off is 1.67 for men and 1.75 for women.
Tampa Scale of Kinesiophobia (TSK) (Kori et al. 1990 [35])	Concerning fear of movement/re-injury 13 items	Scored on a 4 point Likert scale, ranging from 1 (‘strongly disagree’) to 4 (‘strongly agree’). The total score range from 13 to 52. Higher scores indicate higher kinesiophobia
Short Form-12 (SF-12)	Physical and mental health-related quality of life 12-items	Scores ranging from 0 to100. Higher scores reflect better perceived health, with 50 as mean (SD 10) scores for mental and physical dimensions for a healthy population.
Bergen Insomnia Scale (BIS) (Pallesen et al. 2008 [41])	Sleep disturbance 6 items	0–7 days each week. Scored on a 7-point scale; higher scores indicate more severe sleep problems. The total score has a continuous scale (max 42) and normative data has a mean of 10.67 (SD 9.73).

^a^Marked questionnaires are used in the inclusion criteria

**Table 2 Tab2:** Description of the physical tests performed at baseline and 6 month follow-up

Physical tests	Content	Scores
^a^Global Body Examination – Flexibility (GBE) (Kvåle et al. 2012 [43])	Six tests: truncal flexibility and ability to relax during passive movements: Elbow-drop flexibility, lumbar-sacral flexibility, head rotation resistance and resistance to hip circumduction, hip-knee flexion and arm/shoulder flexion	Each test: 0–7. Total score for Flexibility: 0–42, higher score indicating reduced flexibility. Healthy (*n* = 34): Median = 5.5, mean = 7.2.
^a^ACR-tender points (Wolfe et al. 1990 [53])	18 defined fibromyalgia tender points with four kilos pressure are tested.	Painful points are counted
Back Performance Scale (BPS) (Magnussen et al. 2004 [45]; Myklebust et al. 2007 [46])	Five tests reflecting mobility-related activities for trunk and lower extremities (sock-test, pick-up test, roll-up test, fingertip-to-floor and a lift test where a box weighing 4 kg (women) or 5 kg (men) is lifted from floor to waist for 1 min).	Each test: 0–3. Total score: 0–15 with higher scores indicating worse function. Normative data for people without back pain (*n* = 150): Median = 0, mean = 0.8.
High lift test	The high lift test is a modified lift test included in BPS. The participants lift a box of 2 kg (for women) or 3 kg (for men) from waist to shoulder height and back again.	Number of lifts performed in 1 min, are counted.
Biering–Sørensen test (Biering-Sorensen 1984; [47] Keller et al. 2001 [49])	Static endurance of the back. Participants are positioned prone with the upper body extending beyond the edge of the plinth and the lower body is fixed to the bench with three straps.	Seconds keeping the upper body straight are recorded. Max time 240 s. Healthy (*n* = 31): Median = 138 s
Abdominal endurance/strength (Oja et al. 1995 [51])	Three levels of dynamic sit-up test with increased demand for each level. The participants are supine with the knees flexed and with feet supported on the plinth by the tester.	Completed repetitions are counted (0–15).

^a^Marked tests are used in the inclusion criteria

